## Abstract

This study will evaluate subtle morbidity related to infections with *Schistosoma mansoni* and will be part of a bigger study on Gaining and Sustaining Control of schistosomiasis. The study will be conducted in an area of Mwanza Region in Tanzania, where prevalence of *S. mansoni* is 25% or more. The present study will involve the two most extreme of the six study arms of the control study. The primary outcomes of interest will be measured in a cohort of children (7-8 years of age at the initiation of the intervention study) in Years 1, 3 and 5 prior to that year's MDA. A total of 800 children, namely 100 children from 4 randomly selected communities/villages from each subtle morbidity study arm will be enrolled for the 4 years of intervention and the fifth year of follow-up testing. The prevalence and intensity of *S. mansoni* will be determined in Years 1, 3 and 5 as one stool sample on three consecutive days will be examined by duplicate Kato-Katz. Date of birth will be ascertained for all participating children. The following indicators of subtle morbidity will be measured: height and weight, hemoglobin (capillary blood), physical fitness (shuttle run test), symptoms and well-being (PedsQL), Test of Everyday Attention for Children (TEA-Ch), and abdominal ultrasound (only in Years 1 and 5). All children will be treated with mebendazole and an effort will be made to evaluate malaria treatments in the communities. The study will be managed by the National Institute for Medical Research (NIMR), Mwanza, Tanzania and DBL-Centre for Health Research and Development (DBL), Copenhagen, Denmark. The study will take five years to complete and the total budget is 60.000 USD.

## Research goal

The overall goal of this study of subtle morbidity is to provide information to policy- and decision-makers about the impact of MDA with praziquantel in schistosomiasis-endemic areas.

## Methodology

### Study area and population

Investigations of subtle morbidity will be conducted as part of the study on Gaining and Sustaining Control in high prevalence communities. The study area is described in the control proposal (RFP-SCORE-1-3/1.5 2009/Tanzania 2010). The subtle morbidity study will involve two of the six study arms in the main study, which represent the most and least intensive intervention arms. The testing of subtle morbidity will be conducted in Years 1, 3 and 5 prior to that year's annual MDA.

### Study design and sample size

The study population for the Gaining and Sustaining control study will involve repeated cross-sectionals of a random selection of children aged between 9-12 years, first year students (aged  $\leq 8$  years) and adults (aged 20-55 years). For the subtle morbidity studies, the primary outcomes of interest will be measured in a cohort of 7-8 year old children selected at the initiation of the intervention study. 100 children from 4 communities/villages in each subtle morbidity study arm (1 and 2, see figure on next page) will be enrolled in the subtle morbidity studies for the 4 years of intervention and the fifth year of follow-up testing (5 years total). Thus, 800 children will be followed, but testing will only be conducted in Years 1, 3, and 5, prior to that year's annual MDA (arrows on the figure).

Villages for inclusion in this study will be a random sample of the villages in the 2 study arms, but they can be selected from among a restricted group of no less than 10 of the 25 villages in each arm, which could be chosen, for example, for convenience.

[figure not shown]

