### **Project management**

The study will be managed by the National Institute for Medical Research (NIMR), Mwanza Research Centre, Mwanza, Tanzania and DBL-Centre for Health Research and Development (DBL), Faculty of Life Sciences, University of Copenhagen, Denmark.

[name] (AO) will be principal investigator and overall responsible for the financial management of the project. [name] (PM) will assist in the supervision of the project and give technical assistance in the field. [name] (SK) will be overall responsible for the project in the field and train, supervise and support the field staff. SK will be responsible for data collection and quality control. SK conducted his PhD study in Mwanza region and is very familiar with the people, the health staff and health facilities in the area.

**Activities and Timelines (in red, combined with the activities and timelines for the Gaining and Sustaining Control proposal)**

|                                        | 2010 |   |   |   | 2011 |   |   |   | 2012 |   |   |   | 2013 |   |   |   | 2014 |   |   |   | 2015 |   |   |   |
|----------------------------------------|------|---|---|---|------|---|---|---|------|---|---|---|------|---|---|---|------|---|---|---|------|---|---|---|
| Quarter                                | 1    | 2 | 3 | 4 | 1    | 2 | 3 | 4 | 1    | 2 | 3 | 4 | 1    | 2 | 3 | 4 | 1    | 2 | 3 | 4 | 1    | 2 | 3 | 4 |
| Submission for ethical clearance       | X    |   |   |   |      |   |   |   |      |   |   |   |      |   |   |   |      |   |   |   |      |   |   |   |
| Identification of study communities    | X    |   |   |   |      |   |   |   |      |   |   |   |      |   |   |   |      |   |   |   |      |   |   |   |
| Informing of health officials          | X    |   |   |   |      |   |   |   |      |   |   |   |      |   |   |   |      |   |   |   |      |   |   |   |
| Purchase of materials                  |      | X |   |   |      |   |   |   |      |   |   |   |      |   |   |   |      |   |   |   |      |   |   |   |
| Screening of villages for inclusion    |      |   |   |   | X    | X |   |   |      |   |   |   |      |   |   |   |      |   |   |   |      |   |   |   |
| Training of teachers and CHWs          |      |   |   |   |      | X |   |   |      |   |   |   |      |   |   |   |      |   |   |   |      |   |   |   |

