| Randomization                          |      |   |   |   | X    |   |   |   |      |   |   |   |      |   |   |   |      |   |   |   |      |   |   |   |
| Community mobilization                 |      |   |   |   | X    |   |   |   |      |   |   |   |      |   |   |   |      |   |   |   |      |   |   |   |
| Census                                 |      |   |   |   | X    |   |   |   |      |   |   |   |      |   |   |   |      |   |   |   |      |   |   |   |
| Baseline parasitological survey        |      |   |   |   | X    | X |   |   |      |   |   |   |      |   |   |   |      |   |   |   |      |   |   |   |
| Training of study staff                |      |   |   |   | X    | X |   |   |      |   |   |   |      |   |   |   |      |   |   |   |      |   |   |   |
| Morbidity assessments                  |      |   |   |   |      | X |   |   |      |   |   |   | X    |   |   |   |      |   |   |   |      |   | X |   |
| Delivery of treatment                  |      |   |   |   |      | X |   |   | X    |   |   |   | X    |   |   |   | X    |   |   |   |      |   |   |   |
| Follow-up parasitological surveys      |      |   |   |   |      |   |   |   | X    | X |   |   | X    | X |   |   | X    | X |   |   |      |   |   |   |
| Final follow-up parasitological survey |      |   |   |   |      |   |   |   |      |   |   |   |      |   |   |   |      |   |   |   | X    | X |   |   |
| Laboratory work                        |      |   |   |   | X    | X | X | X | X    | X | X | X | X    | X | X | X | X    | X | X | X | X    | X | X | X |
| Collection of cost data                |      |   |   |   |      |   |   |   | X    |   |   |   |      |   |   |   |      |   |   |   |      |   |   |   |
| Health education                       |      |   |   |   |      | X |   |   | X    |   |   |   | X    |   |   |   | X    |   |   |   |      |   |   |   |
| Annual SCORE meeting                   |      |   |   |   | X    |   |   |   | X    |   |   |   | X    |   |   |   | X    |   |   |   | X    |   |   |   |
| Mid-course evaluation                  |      |   |   |   |      |   |   |   |      |   |   |   | X    |   |   |   |      |   |   |   |      |   |   |   |
| Data analysis and report writing       |      |   |   |   |      |   |   |   |      |   |   |   |      |   |   |   |      |   |   |   | X    | X | X | X |

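### The 4 morbidity villages per arm are drawn without stratifying on starting prevalence, so a baseline gap of more than 10 points between the arms is a likely chance event that a two-stratum draw would make much rarer

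*Protocol*

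**What the plan says.** Protocol, Study design and sample size, enrols "100 children from 4 communities/villages in each subtle morbidity study arm" and concludes: "Thus, 800 children will be followed". On how the villages are found it says: "Villages for inclusion in this study will be a random sample of the villages in the 2 study arms". It then allows that "they can be selected from among a restricted group of no less than 10 of the 25 villages in each arm". The Abstract describes the same plain draw: "100 children from 4 randomly selected communities/villages from each subtle morbidity study arm". Neither place mentions stratification, matching or any other balance constraint on prevalence or intensity.

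The Abstract places the study in an area where *S. mansoni* prevalence is at least 25% and gives no ceiling. The timeline under Project management lists "Screening of villages for inclusion" in 2011 Q1-Q2, randomization in 2011 Q1, "Baseline parasitological survey" in 2011 Q1-Q2 and the first morbidity assessments in 2011 Q2. Every cohort child is tested for *S. mansoni* in Years 1, 3 and 5 (Basic data to be collected on all children), before that year's drug administration.

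**The concern.** The comparison of the most and least intensive arms rests on 4 villages against 4. How much a village can gain from treatment depends on how much infection it has at the start. If one arm's villages begin with clearly more infection, a Year 5 comparison and a change-from-Year-1 comparison can be pulled in different directions. The 100 children per village do not help, because the imbalance is between villages.

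The choice of villages is fixed once the cohort is enrolled, and no later analysis plan can change it. It is therefore a design matter that the protocol itself settles. If screening yields a prevalence for each candidate village before the draw, the information needed to limit the imbalance is already available and unused.

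**Working it through.** **Plan's own figure.** 2 arms x 4 villages x 100 children = 800, which reproduces. The protocol gives no effect size, between-village variance or power, so there is no power statement to check.

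**Inputs from the protocol.** 4 villages per arm; a pool of 25 per arm, or a sub-pool of at least 10; a 25% prevalence figure with no ceiling.

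**Assumptions, not in the protocol.** Village prevalence is uniform on 25-65% or on 25-85%, the 25% figure acts as a village floor, and screening prevalence has an error SD of 0 or 7 points.

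**Plain draw, by formula.** The SD of the difference between two means of 4 villages is SD_village x sqrt(1/4 + 1/4) = 0.707 x SD_village. A uniform distribution has SD = range / sqrt(12).

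- 25-65%: SD_village = 40 / 3.464 = 11.5 points. SD of the arm difference = 0.707 x 11.5 = 8.2. By normal approximation, P(gap > 10 points) = 2 x Phi(-10/8.2), about 22%.
- 25-85%: SD_village = 60 / 3.464 = 17.3 points. SD of the arm difference = 12.2. P(gap > 10 points) = 2 x Phi(-10/12.2), about 41%.

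Simulation of the draw gives 22% and 42%.

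**Two-stratum draw, by simulation** (40,000 draws per setting; cut at the common median of screening prevalence, 2 villages per stratum per arm). The gap is measured in true prevalence.

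| Assumed range | Pool per arm | Screening error SD | SD of gap, plain | SD of gap, 2 strata | P(>10), plain | P(>10), 2 strata |
|---|---|---|---|---|---|---|
| 25-65% | 25 | 0 | 8.2 | 4.2 | 22% | 1.5% |
| 25-65% | 25 | 7 | 8.1 | 5.4 | 22% | 6% |
| 25-65% | 10 | 7 | 8.2 | 5.5 | 23% | 7% |
| 25-85% | 25 | 0 | 12.2 | 6.3 | 42% | 11% |
| 25-85% | 25 | 7 | 12.3 | 7.2 | 42% | 17% |
| 25-85% | 10 | 7 | 12.3 | 7.4 | 42% | 18% |

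A pool of 10 gives nearly the same result as 25. The two-stratum draw could not be completed in about 0.1% of pools of 10.

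**Precision if the stratum is modelled.** Let r be the correlation between a village's mean outcome and its prevalence. For the 25-85% case without screening error, the between-village variance of the arm difference falls by about r^2 x (1 - (6.3/12.3)^2) = 0.738 r^2. The 97.5% t quantile rises from 2.447 (6 df) to 2.571 (5 df), a factor of 1.05.

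- r = 0.3: variance cut 7%; interval width factor sqrt(0.934) x 1.05 = 1.015, so 1-2% wider.
- r = 0.5: variance cut 18%; sqrt(0.816) x 1.05 = 0.95, so 5% narrower.
- r = 0.7: variance cut 36%; sqrt(0.639) x 1.05 = 0.84, so 16% narrower.

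These widths concern the between-village component only.

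**The case against.** The strongest reply is that a random sample within randomised arms is unbiased, and that differences between villages are ordinary sampling variance already carried by a village-level standard error. On this view stratifying is an efficiency preference. That is correct: nothing here is bias in expectation. It limits the point to a cheap improvement but does not remove it, because 4 per arm is few and the draw cannot be redone.

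A second reply is that infection is measured in every child in Year 1, so the analysis can adjust. This stands in part. With 8 villages, adjusting for a village-level imbalance is only a partial remedy, and change from baseline does not make arms with different starting infection comparable if the starting level limits the benefit.

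A third reply is that the precision gain is modest. This also stands: at a correlation of 0.3 the lost degree of freedom uses it up.

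Two stronger readings should be resisted.

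- A reader might infer that the treatment contrast will be halved or inflated. The protocol gives no effect size or between-village variance, so this cannot be derived from it. Assume a village SD of 14.4 points and a true final prevalence contrast of 20 points. The chance that an unadjusted contrast is cut to half or less is then Phi(-10 / (0.707 x 14.4 x c)), where c is the share of baseline imbalance that carries over. It is 16% at c = 1, 2.5% at c = 0.5 and under 0.1% at c = 0.25. The answer comes almost entirely from the assumption.
- A reader might infer that each village's prevalence is known before the draw. The protocol does not say what screening measures, and screening runs into the quarter after the one listed for randomization. It is a fair inference, to be confirmed.

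Eligibility and any stratification of the main randomization are left to the control proposal, which is not at hand. Stratifying the 25 villages per arm would not by itself balance a sub-sample of 4.

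**Conclusion.** The point holds as a worthwhile, low-cost design improvement. The protocol fixes an unstratified draw of 4 villages per arm. Under assumed village ranges of 25-65% to 25-85%, the arms differ by more than 10 points in starting prevalence in about 22-42% of draws. Two strata lower this to about 6-18% with an assumed 7-point screening error. The sizes rest on the assumed uniform spread and screening error, neither of which the protocol gives. The imbalance is chance variance, and the gain in precision ranges from none, for outcomes weakly tied to prevalence, to appreciable for outcomes strongly tied to it.

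**What to change.** In Study design and sample size, and in the Abstract, replace the plain draw with a stratified one:

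- Confirm first that screening yields a prevalence for each candidate village and that the results are available before the draw.
- Pool the eligible villages of both arms (all 25 per arm, or the sub-pools of at least 10 if that option is used) and cut at their common median screening prevalence.
- In each arm, draw 2 villages at random below the cut and 2 above it.
- Record the stratum for the analysis.

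Two strata are enough. With one village from each of four strata and a pool of 10, about 11% of draws would leave a stratum empty in one arm (assumed range 25-90%).

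Cost: a sentence of text and a different draw list, with no extra villages or children. Screening must be complete before the draw, which the timeline does not guarantee. If the stratum is modelled, 1 of 6 village-level degrees of freedom is lost.

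### The morbidity villages may come from a convenience-chosen subset of each arm with no common arm-blind rule, so randomisation no longer guarantees that the 4-versus-4 village comparison is like with like

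*Protocol*

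**What the plan says.** The abstract describes the cohort as "100 children from 4 randomly selected communities/villages from each subtle morbidity study arm" and mentions no restriction on the villages eligible for the draw.

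The section on study design and sample size begins the same way: "Villages for inclusion in this study will be a random sample of the villages in the 2 study arms". The same sentence then allows the draw to be made from a "restricted group of no less than 10 of the 25 villages in each arm, which could be chosen, for example, for convenience". The permission is optional. The section gives no criterion beyond convenience as an example. It does not say who forms the group, whether that person sees the allocation, or whether the two arms must be restricted in the same way.

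The two arms are the most and least intensive of the six in the parent control study (study area and population). In the timeline, "Randomization" is marked for the first quarter of 2011 and the first morbidity assessment for the second quarter. No row shows when the morbidity villages are chosen.

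**The concern.** Randomising 25 villages to each arm makes the two sets comparable in expectation. A later subsample keeps that property if the way it is taken does not depend on arm. The final random draw makes the 4 villages representative of the restricted group they came from. It does not make them representative of the 25 that were randomised. If the two groups are formed by different criteria, the arms may differ before any treatment is given, and the random draw does not repair this.

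What makes a village convenient is not defined. Ease of access, for instance, could plausibly go with wealth or use of health services, which bear on haemoglobin, growth and fitness. A Year 5 difference could then partly reflect which villages were chosen in each arm and not the intensity of mass drug administration (MDA). Enrolling 100 children per village does not reduce such a bias, because it arises at village level. With 8 villages in all there is little room to correct it by village-level covariate adjustment. The stated goal is to inform policy-makers about the impact of MDA, so the contrast between arms is what has to be protected.

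**Working it through.** **The protocol's own figure.** "100 children from 4 communities/villages in each subtle morbidity study arm" over two arms gives 2 × 4 × 100 = 800, which agrees with "Thus, 800 children will be followed". No power calculation is stated, so there is none to reproduce.

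**Inputs from the protocol.** 25 villages per arm; restricted group of at least 10; 4 villages drawn per arm; 100 children per village.
- Villages that can be set aside: (25 − 10)/25 = 60% per arm.

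**Assumptions, not in the documents.** Village means are normally distributed; the ICC is 0.02 to 0.10; the correlation *r* between convenience and village mean is 0.3 to 0.5; the restricted group is the most convenient 40%.

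**Bias in a cross-sectional comparison.** The mean of the top 40% of a standard normal is 0.966. With total child-level SD 1, one village SD is √ICC. The expected difference between arms with no treatment effect is

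bias = 0.966 × (r_A − r_B) × √ICC.

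If only arm A's choice is related to outcome (r_B = 0), in child-level SD:

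| ICC | r = 0.3 | r = 0.5 |
|---|---|---|
| 0.02 | 0.041 | 0.068 |
| 0.05 | 0.065 | 0.108 |
| 0.10 | 0.092 | 0.153 |

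If the same rule is used in both arms, r_A = r_B and the bias is zero. If both arms favour convenient villages but to different degrees (0.5 and 0.3), it is 0.966 × 0.2 × √ICC = 0.03 to 0.06 SD.

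**Check with the actual village numbers.** A simulation with 40,000 runs per setting used 25 villages per arm and no treatment effect. It kept 10 villages per arm on the convenience score, drew 4 of them at random, and applied a two-sided 5% t-test to the village means:

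| Setting | Bias (village SD) | Type I error |
|---|---|---|
| Restriction unrelated to outcome in both arms | −0.004 | 0.050 |
| Same rule in both arms, r = 0.5 | 0.002 | 0.053 |
| One arm only, r = 0.3 | 0.284 | 0.063 |
| One arm only, r = 0.5 | 0.472 | 0.095 (0.092 in a second run) |

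The factor implied for 10 of 25 villages is 0.472/0.5 = 0.94, slightly below 0.966. The range is unchanged after rounding: 0.94 × 0.3 × √0.02 = 0.04 and 0.94 × 0.5 × √0.10 = 0.15.

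With r = 0.5 in one arm, keeping 15, 20 or all 25 villages gives a bias of 0.317, 0.170 or −0.001 village SD and a type I error of 0.070, 0.054 or 0.052. The problem fades as the restriction is relaxed.

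**Scale.** The standard error of a 4-versus-4 difference in village means is √(2/4) = 0.71 village SD, before sampling noise among children. The one-arm bias of 0.284 to 0.472 is therefore 0.40 to 0.67 of a standard error. The simulation leaves out child-level noise. With 100 children that noise adds (1 − ICC)/100 to the variance of a village mean, so at ICC 0.02 the bias relative to the standard error shrinks by √(0.02/0.0298) = 0.82, and at ICC 0.10 by √(0.10/0.109) = 0.96. The type I errors above are thus slightly high, more so at low ICC.

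**The case against.** Four points on the other side carry weight.

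- **The permission is optional and may be meant as one rule.** The wording also fits a single restriction, such as one accessible area, with a floor of 10 villages left in each arm. A reader might infer that the groups will be picked separately, within lists already labelled by arm and after allocation. That is a natural inference from the phrase about each arm and from the order of the timeline, but the protocol does not state it. This stands, and it limits the claim to what is not guaranteed.
- **A common rule does no harm to comparability.** The calculation confirms this: bias is near zero and type I error is 0.053. Only representativeness suffers. This also stands.
- **Year 1 measurements before MDA exist for the same children on every core indicator, ultrasound included.** Stable village differences largely cancel in change from Year 1, and a change score uses no village-level degrees of freedom. The figures above are for cross-sectional means and overstate the bias in such an analysis. What remains is any village factor that alters the course over the following years, which baseline values do not remove.
- **The abstract omits a detail and does not contradict the methods.** Villages drawn at random from a smaller list are still randomly selected. This is fair: the wording needs aligning, but there is no outright conflict.

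These points reduce the size and certainty of the problem. They do not supply the missing safeguard. The selection rule is a design step fixed in this document, and no analysis plan can change which villages were chosen.

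**Conclusion.** The point holds in a limited form. The protocol explicitly allows a non-random restriction to as few as 10 of 25 villages per arm and does not require it to be the same, or blind to allocation, in both arms. Randomisation therefore no longer guarantees comparability if the restriction differs by arm. Under the assumed ICC of 0.02 to 0.10 and correlation of 0.3 to 0.5, a choice related to outcome in one arm only gives a cross-sectional bias of about 0.04 to 0.15 child-level SD, with type I error of about 0.06 to 0.09 in place of 0.05. The bias is smaller for change from Year 1 and near zero under a common rule.

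Three stronger conclusions are tempting but unsupported:
- that the protection of randomisation is lost outright, since that depends on how an optional permission is used;
- that the bias could be twice as large (0.08 to 0.31 SD), since this needs the arms restricted in opposite directions, which a choice for convenience gives no reason to expect;
- that the bias matches the effect the study expects to see, since the protocol states no expected effect.

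This is an under-specified safeguard in a comparison of only 8 villages. It is worth closing because it is cheap to close and cannot be repaired once villages are enrolled.

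**What to change.** In the section on study design and sample size, replace the convenience permission with one written feasibility criterion. It should be set before allocation, or by someone without sight of it, and applied identically to both arms. Draw the 4 villages per arm at random from all villages that meet it, or from all 25 where that is feasible, and report which villages were excluded and why. Reword the abstract so that its account of random selection names the same list of eligible villages.

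The cost is one or two sentences, slightly less freedom in choosing villages, and possibly some extra travel. Drawing from all 25 villages is the cleaner option but may strain the budget: field costs are set at 4,440 USD per testing year, and each child gives stool on three consecutive days. The common criterion secures comparability without requiring that. Stratifying so few villages by screening prevalence would be a matter of preference and is not needed here.
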